##### Online psychological treatment

An online treatment program, based on value-based cognitive behavioral therapy, was specifically developed for the study. The psychologist will contact the patient who is referred by the nursing staff and organise an intake over the phone. During the intake – which is similar to the standard intake when the psychologist meets with the patient face-to-face for the first time – the patient and the psychologist discuss how the patient is doing and what might have contributed to the onset of anxiety or depression. If the patient feels impaired in his / her daily living and consents to start with treatment, the psychologist will initiate treatment that consists of 7 steps: *(i)* ICD and its impact; *(ii)* When one’s life changes; *(iii)* The impact of thoughts on mood and actions; *(iv)* Acceptance and values – living a valuable life; *(v)* How does my daily life looks like?; *(vi)* Find a good routine; *(vii)* To continue to develop and accept stagnation or relapse. If the patient has already contacted or is being seen by a psychologist, the patient will not be offered parallel treatment in the ACQUIRE-ICD study. In order to increase patient compliance with the psychological treatment, patients are offered a phone consultation mid-way (Step 3) and towards the end (Step 7) of the psychological treatment. If patients screen positive for anxiety and / or depression again, the patient will again be referred to the psychologist.

##### Dialogues with nursing staff via the platform

Dialogues via the platform with nursing staff happen asynchronously. The patient can always enter data and see on the platform when the nurse will send a message or respond to the patient’s message. During the first 3 months of the intervention, the nurse will send weekly messages, while in months 4–12, there will be one message a month. Additional messages are allowed on a need-to-basis.

##### Information provision and education

To support behavioural change and to enhance patient motivation and compliance, a toolbox is developed that contains educational multimedia content, such as vodcasts, links, text and pictures, e.g. from *‘Helbredsprofilen’*
https://helbredsprofilen.dk/en. The toolbox that was developed for the ACQUIRE-ICD study has a broad focus with topics on ICD treatment and management, self-care management, resources for lifestyle changes and management (e.g. exercise tips), how to set realistic goals, how to keep up motivation, and psychological and social issues, etc. The toolbox also contains quizzes to inform and test patients’ knowledge and educate them about their device, heart disease, psychological aspects and related topics. In order not to overwhelm patients with too much or irrelevant information, nurses will send the contents of the tool box to patients on the times scheduled for contact via the nursing dialogues mentioned above according to a pre-specified plan based on clinical experience and when patients may need the information. These supportive tools can be tailored to the individual needs of patients.

##### Forum with online community network

This feature was included in the intervention, as evidence has shown that online communities with peer-to-peer support from “*patients like me*” that allow for patients to share their stories and experiences is a successful addition to web-based and digital solutions to facilitate behavioural change and to provide social support, as it makes patients feel less alone [44]. The community is part of a mature community with more than 1000 members and will undergo a mitosis after the inclusion of 50 patients to strengthen the domain of ICD patients [45]. As there is a known trade-off between moderation and control on online patient communities and as we wanted to ensure that patients feel free to express and share their thoughts and experiences freely, we decided moderation only by a “watchdog” – the community manager of the project team – who follows the discussions on the forum and redirect the conversation positively if it goes in a less helpful manner [46].

### Sample size calculation

Based on historical data from the Web-based Distress Management Program for Implantable Cardioverter Defibrillator (WEBCARE) patients that evaluated the effectiveness of an online behavioural treatment based on problem-solving principles of cognitive behavioural therapy [47, 48], we assume that a difference in device acceptance, as measured by the Florida Patient Acceptance Survey, of 3 points at 12 months is the minimal clinically relevant difference between treatment groups. We further assume a standard deviation (SD) of 9 points. Targeting the power analysis to these assumptions, with a type I error of 0.05 (two-sided) and a power of 90%, 382 patients need to be evaluable for the primary endpoint. To compensate for loss to follow-up (estimated at 20%), we will aim to randomise a total of 478 patients (239 in each arm).

### Randomisation, blinding and treatment allocation

Patients are randomised in a 1:1 fashion to the ACQUIRE-ICD eHealth intervention plus usual care versus usual care alone, stratifying by center and heart failure symptom severity (New York Heart Association (NYHA) functional class I-II versus III-IV). A random allocation sequence will be generated for each stratum by an independent statistician. The sequence determines the allocation for each subsequent patient. It is not possible to blind patients as to their study condition.

### Ethics and safety considerations

The study will be conducted according to the principles of the Declaration of Helsinki (64th WMA General Assembly, Fortaleza, Brazil, October 2013). The study protocol was submitted to the Regional Committees on Health Research Ethics for Southern Denmark, who indicated that according to Danish law about ethics related to health research (§ 14, 1), ethical committee approval is not required (VEK #S-20160063, June 13, 2016). The Danish Data Protection Agency, via the umbrella scheme in the Region of Southern Denmark (OUH #16/16935, June 21, 2016), has approved the project. Permission from the Danish Health Authority is normally required if information from patients’ EHRs need to be used for specific research projects (health law § 46, 2). However, this is not required if patients provide written consent that they are willing to pass on this information, as is the case for ACQUIRE-ICD. The trial has been registered on https://clinicaltrials.gov/ct2/show/NCT02976961 [NCT02976961].

### Statistical methods

#### General analyses

Data will be analysed according to the modified intention-to-treat principle (i.e., all patients with a 12-month evaluation will be analysed as randomised). Categorical variables will be summarised as n (%), continuous variables as min-max, mean (SD), and median. All summaries will be reported by randomisation group. Kaplan-Meier models will be used to estimate survival functions related to time-to-event endpoints e.g. mortality, stratified by group. Regression analyses, linear, logistic, and Cox proportional hazard will be used as appropriate. The type of analysis will depend on the endpoint in question. The primary analysis will be a linear regression of patients’ scores on the Florida Patient Acceptance Survey at 12 months including randomisation group, baseline score and strata as factors and patients’ Florida Patient Acceptance Survey scores at baseline as covariates. Potential confounders, apart from baseline and stratification variables, identified by clinical consensus, will be included in multivariable analyses when appropriate (e.g. when performing sub-group analyses). Additionally, a mixed effects model will be used to analyse the longitudinal change in mean device acceptance scores on the Florida Patient Acceptance Survey while adjusting for strata and baseline Florida Patient Acceptance Survey scores, incorporating random effects to model the homogeneity within cluster and the correlation within patient across time.

Subgroup analyses are planned for the primary endpoint with respect to: Type of device (CRT-D versus ICD); symptomatic heart failure (NYHA class I-II (mild) versus NYHA class III-IV (severe)); indication (primary versus secondary prevention); sex (female versus male); age (median split); depression status (PHQ score < 9 versus ≥10). All other subgroup analyses are explorative.

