#### Secondary endpoints

Secondary endpoints include health status (generic and disease-specific), patient empowerment, ICD concerns, anxiety, depression, return to work, time to first ICD therapy defined as ATP or shock, time to first hospitalisation due to a cardiac cause, mortality, resource use and costs related to the intervention, additional healthcare resource use and costs during the observation period, and cost-effectiveness. All secondary endpoints are evaluated at 12 and 24 months’ post implant. Primary and secondary outcomes are presented in Table 1.

**Table 1 Tab1:** Primary and secondary endpoints

Primary outcome *[evaluated at 12 months’ post implant]* • Device acceptance (FPAS) Secondary outcomes *[evaluated at 12 and 24 months’ post implant]* • Health status (SF-12) • Patient empowerment (ICD-EMPOWER) • ICD concerns (ICDC) • Anxiety (GAD-7) • Depression (PHQ-9) • Health status (KCCQ-12; for patients with heart failure only) • Return to work • Time to first ICD therapy defined as anti-tachycardia pacing, cardioversion or shock • Time to first hospitalisation due to a cardiac cause • Mortality • Cost of intervention program • Healthcare costs • Labour market absence • Cost-effectiveness (i.e., incremental cost gained per quality adjusted life year (QALY) and burden on health care professionals (physicians and nurses)^a^	

^a^This will be measured with the EQ-5D-5 L or captured from the patient’s electronic health record (EHR; e.g. number of outpatient visits, admissions, consultations with psychologists), and purpose-designed questions

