Effect, in terms of changed/increased life expectancy, will be estimated based on extraction of vital status from the National Death Registry. This registry includes date of death and recorded casus of death if that has occurred.

In addition, data from the National registry on Social Transfer Payment (DREAM) will be obtained. This registry will provide data on long-term sickness and reimbursement of lost productivity and provide a measure of the absence from the labour market. This will only be relevant for the period that participants are affiliated with the labour market (i.e. until retirement age). The registry will also provide information about early sickness and voluntary retirement (i.e. before retirement age). Difference between the participant groups will be analysed using logistic or time-to-event regression methods. Additional costs in terms of short-term productivity costs due to absence from the work force (# missed workdays patients; # missed workdays caregivers; # hours care giving to patient) will be obtained through participant questionnaires. Labour market absence will be valued using age and gender stratified by average gross wages obtained from Statistics Denmark.

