#### Cost-effectiveness analyses

The analysis of resource use and costs will be conducted on individual participants’ aggregated cost measures during the observation period (12/24 months) from the inclusion date for each individual participant. Cost data are usually skewed and therefore require special analytical methods. The analysis will use the current standard methodology for cost data (generalised regression assuming logistic link function and residuals with gamma distribution). Other methods will be explored to identify the specifications that provide better fit to the data.

All-cause mortality, survival time, retirement and time to retirement will be estimated from inclusion date until death or censoring using appropriate statistical models (Cox-regression or similar). All-cause and cardiac-related mortality will also be used as measures of effect in the cost-effectiveness analysis.

Quality-adjusted life years (QALYs) will be estimated for each individual participant using all the available data points from the EQ-VAS and EQ-5D instrument. The EQ-5D scores will be converted to utility measures (index ranging from 0 to 1) using the recommended algorithm. Work is currently in progress to establish an updated Danish value set. The analysis will be based on the most updated value set at the time of analysis. Sensitivity analysis will be conducted using different value sets. The QALYs will include the area “under the curve” of the different data points during the observation period or until death.

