The cost-effectiveness/cost-utility analysis generates results in terms of incremental cost-effectiveness ratios (ICERs). This analysis will use the data set of individual participants’ monitarised resource use (cost) and QALY. Mixed level difference-in-difference modelling will identify the average incremental cost and effect of the intervention in comparison with the control group (the ICER). By assuming a society treshold value for health benefits (QALYs), the net monetary value of the intervention will be analysed for the whole study population (intention-to-treat and per-protocol) and subgroups of the population. In order to assess the precision, the ICERs sensitivity analysis (relating to structural uncertainty) and bootstrapping methods (relating to statistical/parameter uncertainty) will be performed. Both a short-term and a long-term cost-effectiveness analysis (CEA) will be performed. The short-term CEA will use 12/24 months’ time horizon (equivalent to the two-year follow-up period) based on the data obtained through the trial. The long-term CEA will have a lifetime time horizon and will employ a purpose-built model of health outcomes and resource use. The model will extend both cost and effect data obtained from the trial using appropriate statistical methods. Analyses of the CEA will include probabilistic analyses, sensitivity analyses, and scenario analyses. The main cost-effectiveness results will be described as the incremental cost per QALY gained and net-monetary benefit.

Before release of the data for analyses, the statistician involved in the project will write a detailed statistical analysis plan that will be subject to review and approval by the steering committee. Data will be analysed using STATA and R via OPEN Analyse, which is an analysis environment (platform), where data can be stored and processed securely on a server, which is in compliance with the General Data Protection Regulation Directive 95/46/EC.

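### The 12-month-evaluation analysis set is stated for all data, so as written it also governs mortality and the other time-to-event endpoints

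*Protocol article*

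**What the plan says.** All references are to the Protocol article.

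- **General analyses** opens with the rule on the analysis set: "Data will be analysed according to the modified intention-to-treat principle (i.e., all patients with a 12-month evaluation will be analysed as randomised". The subject is data in general; no endpoint is named.
- The same paragraph goes on to the event-time methods: "Kaplan-Meier models will be used to estimate survival functions related to time-to-event endpoints e.g. mortality, stratified by group", and then "Regression analyses, linear, logistic, and Cox proportional hazard will be used as appropriate". Neither sentence gives a different population.
- **Secondary endpoints** lists "time to first ICD therapy defined as ATP or shock, time to first hospitalisation due to a cardiac cause, mortality" and adds that "All secondary endpoints are evaluated at 12 and 24 months".
- **Cost-effectiveness** says that the effect on life expectancy "will be estimated based on extraction of vital status from the National Death Registry". **Demographic and clinical variables** says that follow-up events come from electronic health records, also for patients who drop out, provided that they consent.
- **Cost-effectiveness analyses** reads differently from General analyses: "All-cause mortality, survival time, retirement and time to retirement will be estimated from inclusion date until death or censoring", and "the net monetary value of the intervention will be analysed for the whole study population (intention-to-treat and per-protocol".

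**The concern.** Having a 12-month evaluation is something that happens after randomisation. A questionnaire score at month 12 exists only for patients who reach month 12 and respond, so the rule has a natural meaning there. A survival endpoint is different: the patient who dies in month 4 is the observation of interest, and on the plain reading the rule removes that patient.

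Three consequences follow if the rule is applied as written:

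1. Mortality at 12 months is zero in both arms by definition of the set.
2. The 24-month mortality curves start with a year in which nobody in the set can die (immortal time).
3. ICD therapies and cardiac hospitalisations are lost for every patient who later dies or is lost before month 12. Events in patients who do reach the evaluation are kept.

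If early death or dropout differs between the arms, the comparison is no longer protected by randomisation. A difference in dropout is plausible here: the trial is unblinded, and only the intervention arm receives weekly and later monthly messages from a nurse.

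**Working it through.** **1. Which text covers which endpoint**

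| Endpoint | Set under General analyses | Other wording in Cost-effectiveness analyses |
|---|---|---|
| Mortality | 12-month evaluation, no exception | Followed from inclusion to death or censoring |
| Time to first ICD therapy | 12-month evaluation, no exception | None |
| Time to first cardiac hospitalisation | 12-month evaluation, no exception | None |
| Net monetary value | 12-month evaluation, no exception | Whole study population |

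General analyses names only mortality; the other two endpoints enter because Secondary endpoints defines them as times to a first event. Nothing in the economic section says that it replaces the general set for the clinical endpoints.

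**2. The plan's own figures (Sample size calculation)**

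Inputs: difference 3 points, SD 9 points, two-sided alpha 0.05, power 90%, loss 20%.

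- Normal approximation: n per arm = 2 × (1.960 + 1.2816)² × 9² / 3² = 189.1, so 190 per arm and 380 in total.
- With the noncentral t distribution: 191 per arm, 382 in total, power 0.901. This matches the stated 382.
- 382 / 0.80 = 477.5, so 478. This matches as well.
- Patients planned to be without a primary-endpoint value: 478 − 382 = 96.

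**3. Size of the effect on deaths (illustration)**

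The documents give no mortality rate. Assume annual mortality m of 2%, 5% or 10%, constant over time and equal in both arms.

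- Deaths by 12 months: D12 = 478 × m
- Deaths by 24 months: D24 = 478 × [1 − (1 − m)²]
- Case A, only early deaths lack the evaluation: share of 24-month deaths excluded = D12 / D24 = 1 / (2 − m)
- Case B, the set shrinks to the planned 382, all alive at month 12: deaths kept = 382 × m, share excluded = 1 − 382m / D24, and apparent 24-month mortality = m instead of 1 − (1 − m)²

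| m | D12 | D24 | Case A: share excluded | Case B: deaths kept | Case B: share excluded | 24-month mortality, all randomised vs set |
|---|---|---|---|---|---|---|
| 2% | 9.6 | 18.9 | 51% | 7.6 | 60% | 3.96% vs 2.0% |
| 5% | 23.9 | 46.6 | 51% | 19.1 | 59% | 9.75% vs 5.0% |
| 10% | 47.8 | 90.8 | 53% | 38.2 | 58% | 19.0% vs 10.0% |

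That no first-year death remains follows from the set itself and needs no assumed rate. For ICD therapy and cardiac hospitalisation the documents give no event rates, so the number of lost events cannot be calculated.

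**The case against.** The best defence is that the article never defines a 12-month evaluation. Secondary endpoints says that every secondary endpoint, mortality included, is evaluated at 12 and 24 months, and Table 2 schedules registry-based mortality at 12 months. On that usage, a patient found dead in the registry at month 12 has been evaluated. The literal reading also empties a declared endpoint, which the authors can hardly have wanted, and the economic section shows that they think of survival from inclusion onwards. Finally, this is a condensed article that promises a detailed statistical analysis plan, where endpoint-specific sets normally belong.

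Part of this stands. What the authors intended is open, and for mortality the document is better called contradictory than uniformly wrong. The rest does not remove the point. If a registry check counted as an evaluation, nearly everyone would qualify and the modification of intention-to-treat would have little meaning. The economic wording does not extend to ICD therapy or cardiac hospitalisation. And the matter is not a detail left for later: a rule is stated, it gives a wrong result for these endpoints, and an analysis plan that follows it would inherit the error.

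A reader might go further and infer that all registry analyses, including costs and labour-market absence, lose the early deaths, and that 96 patients with complete follow-up are thrown away. The documents do not support this. The cost and labour-market analyses may already escape through the economic section. No text says that follow-up of those 96 is complete: the 20% loss is not broken down, and health-record capture depends on consent.

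**Conclusion.** The point holds for the secondary time-to-event endpoints. As written, General analyses conditions mortality, first ICD therapy and first cardiac hospitalisation on a post-randomisation event, and the economic section contradicts it for mortality without resolving it. Mortality could therefore be reported on two populations within one trial.

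At an assumed annual mortality of 2% to 10%, about 10 to 48 first-year deaths would be excluded, which is 51% to 53% of the deaths by 24 months, or 58% to 60% if the set shrinks to 382. These figures rest on a constant rate that is equal in both arms. They measure lost events; they do not show a bias in either direction, which would need a difference between arms in early death or dropout. The primary endpoint and the sample size of 478 are not affected.

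**What to change.** - Limit the 12-month-evaluation set to the questionnaire endpoints.
- State that mortality, time to first ICD therapy and time to first cardiac hospitalisation are analysed in all randomised patients, in the arm to which they were allocated. Each patient is followed from randomisation to the event, withdrawal of consent for data, or the end of registry or health-record follow-up, whether or not a 12-month questionnaire exists.
- Reconcile General analyses with Cost-effectiveness analyses so that mortality is reported on one population.

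The cost is one or two sentences in the protocol, carried into the analysis plan that the article says will be written before data are released. No new data collection is needed, because deaths come from the national registry and events from health records that are already being captured. The sample size does not change.

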### Study endpoints

#### Primary endpoint

The primary endpoint is patient device acceptance measured with the Florida Patient Acceptance Survey [33, 34], evaluated at 12 months’ post implant.

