#### Patient-reported measures

An overview of the patient-reported measures and related measures and their time of administration are shown in Table 2. All measures are standardised and validated, although purpose-designed questions or questionnaires have been added if relevant and when no validated measure was available (e.g. in relation to the assessment of cost-effectiveness and patient empowerment).

**Table 2 Tab2:** Patient-reported outcomes, cost-effectiveness and their assessment*

Construct	Scale acronym	Items	*T* _0_	*T* _6_	*T* _12_	*T* _24_
Health status (generic)	SF-12	12	X	X	X	X
Health status (HF specific)	KCCQ	12	X	X	X	X
Depression	PHQ-9	9	X	X	X	X
Anxiety	GAD-7	7	X	X	X	X
Expectations to ICD treatment	EXPECT-ICD	10	X			
Expectations to use of platform/app	EXPECT-APP	6	X			
Experience with use of platform/app	EXPERIENCE-APP	9		X	X	
ICD patient concerns	ICDC	8	X	X	X	X
ICD empowerment	ICD-EMPOWER	14	X	X	X	X
Illness perceptions	B-IPQ	9 + 1	X			
Adherence	MMAS-8	8	X	X	X	X
Type D personality	DS14	14	X			
Device acceptance	FPAS	18	X	X	X	X
Loneliness	UCLA	3	X	X	X	X
Cost of intervention program	€	Registry	X	X	X	X
Healthcare cost during observation period	€	Registry	X	X	X	X
Labour market absence	€	Registry	X	X	X	X
All-cause and cardiac-related mortality	Deaths	Registry	X	X	X	X
QALY	EQ-5D-5 L + VAS	6	X	X	X	X
Cost-effectiveness/utility (ICER)	€/QALY	–	X	X	X	X
Net-monetary benefit from health care and social perspective	€	-	X	X	X	X

*T*_*0***=**_ Baseline*;*
*T*_*6*_ *=* 6 months*;*
*T*_*12*_ = 12 months*;*
*T*_*24*_ = 24 months

^*^*Both patients in the treatment group and usual care group will complete all measures at*
*T*_*0,*_*T*_*6,*_*T*_*12,*_ and *T*_*24*_

*B-IPQ* Brief Illness Perceptions Questionnaire, *DS14* Type D Scale, *EQ-5D-5 L* EuroQoL, *EXPECT-ICD* Expectations to ICD treatment questionnaire, *EXPECT-APP* Expectations towards use of app, *EXPERIENCE-APP* Experience with use of app, *FPAS* Florida Patient Acceptance Survey, *GAD* Generalised Anxiety Disorder scale, *ICD-EMPOWER* ICD Empowerment Scale, *ICDC* ICD Patients’ Concerns Questionnaire, *KCCQ* Kansas City Cardiomyopathy Questionnaire, *MMAS-8* Morisky Medication Adherence Scale, *PHQ-9* Patient Health Questionnaire, *QALY* quality adjusted life year, *SF-12* Short Form Health Survey, *UCLA* UCLA Loneliness Scale, *VAS* visual analogue scale

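### The primary FPAS analysis keeps only patients with a 12-month evaluation and leaves out the 6-month score, so it is biased if loss follows post-baseline acceptance differently by arm

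*Protocol article*

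**What the plan says.** All references are to the protocol article.

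- **Primary endpoint:** "The primary endpoint is patient device acceptance measured with the Florida Patient Acceptance Survey", evaluated at 12 months.
- **General analyses, population:** a modified intention-to-treat set in which "all patients with a 12-month evaluation will be analysed as randomised".
- **General analyses, primary model:** "The primary analysis will be a linear regression of patients’ scores on the Florida Patient Acceptance Survey at 12 months", with arm, strata and baseline FPAS as the other terms. There is no 6-month term.
- **General analyses, longitudinal model:** "Additionally, a mixed effects model will be used to analyse the longitudinal change in mean device acceptance scores". It is named as an extra analysis. The restriction to patients with a 12-month evaluation is written for the data in general, and nothing exempts this model from it.
- **Patient-reported measures, Table 2:** FPAS is scheduled at every visit. The footnote reads "Both patients in the treatment group and usual care group will complete all measures at" baseline, 6, 12 and 24 months.
- **Sample size calculation:** the target is a difference "of 3 points at 12 months is the minimal clinically relevant difference between treatment groups", with SD 9, two-sided 5% and 90% power. The number is then raised for an expected 20% loss to 478.

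**The concern.** A regression on 12-month completers is valid only if, given arm, strata and baseline FPAS, being lost tells nothing more about the 12-month score. What happens to the patient after baseline may break that condition.

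The setting makes this plausible. Patients know their arm, and the Discussion accepts that lack of blinding may bias the effect. Only one arm has a year of monthly symptom questionnaires, weekly and later monthly nurse messages, and possible referral for psychological treatment. The section on symptom monitoring itself describes depression and anxiety as possible barriers to compliance. Patients who adapt poorly could therefore leave the two arms at different rates or for different reasons.

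At stake are the headline estimate, its p-value and its comparison with the 3-point difference. Randomising more patients restores power after loss but does not remove bias. The 6-month FPAS is the most direct collected evidence on how later dropouts were adapting, and the primary model does not use it.

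**Working it through.** **1. The plan's own figures.** Inputs from the sample size section: difference 3, SD 9, two-sided alpha 0.05, power 90%, loss 20%.
- Normal approximation: n per arm = 2 × (1.96 + 1.2816)² × 9² / 3² = 2 × 10.51 × 9 = 189.1, so 190. The exact two-sample t-test needs 191 per arm, which gives 382 in total.
- 382 / (1 − 0.20) = 477.5, so 478. Both stated figures reproduce.
- Expected outside the primary analysis: 478 − 382 = 96 patients, or 20%.

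**2. What creates bias.** In one arm let π be the proportion lost, and g the mean 12-month FPAS of stayers minus that of leavers, at the same baseline score. The full mean is (1 − π) × stayers + π × leavers, so the completer mean is too high by π × g. Therefore

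bias in the arm difference = π_I × g_I − π_C × g_C (I = intervention, C = usual care).

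With an illustrative gap of 3 points:
- Same gap in both arms, loss 20/20: 0.20 × 3 − 0.20 × 3 = 0.
- Same gap in both arms, loss 25/15 (intervention/usual care): (0.25 − 0.15) × 3 = 0.30.
- Gap in the intervention arm only, loss 20/20: 0.20 × 3 = 0.60.
- Gap in the intervention arm only, loss 25/15: 0.25 × 3 = 0.75.
- No gap given baseline: 0, however unequal the loss.

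**3. Size under explicit assumptions.** SD 9 is from the protocol. The rest is assumed: correlations 0.60 (baseline with 6 months), 0.51 (baseline with 12 months) and 0.66 (6 with 12 months), and a log-odds of loss that rises by 0.5 or 1 per SD of lower 6-month FPAS. True effect is zero. Results for the completer regression:

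| Loss depends on 6-month FPAS in | Slope | Loss I/C | Bias (points) | Type I error |
|---|---|---|---|---|
| intervention arm only | 1 | 25/15 | +0.70 | 14% |
| intervention arm only | 1 | 20/20 | +0.56 | 11% |
| intervention arm only | 0.5 | 23/17 | +0.36 | 7% |
| both arms | 1 | 25/15 | +0.26 | 6.3% |
| both arms | 0.5 | 25/15 | +0.15 | 5.4% |
| both arms | 0.5 | 23/17 | +0.08 | 5.1% |
| both arms | 0.5 | 20/20 | 0 | 5.0% |

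Check of the first row: the standard error is 0.782, so the shift is 0.695 / 0.782 = 0.89 standard errors. P(Z > 1.96 − 0.89) + P(Z < −1.96 − 0.89) = 0.142 + 0.002, about 14%. As a share of the target, 0.70 / 3 = 23%.

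**4. Unequal loss alone.** With a true effect of 3 and assumed correlations 0.6, 0.6 and 0.7, loss of 25/15 or 30/10 that was random or depended on baseline FPAS gave completer estimates of 2.96 to 3.02, so no bias.

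**5. What the 6-month score repairs.** If every lost patient has a 6-month FPAS, an analysis that uses it leaves a bias within about 0.02 in the settings where loss follows the 6-month score. Two limits apply.
- In the first row of the table, if half of the lost patients also lack the 6-month score, about +0.3 remains. If three quarters lack it, about +0.5 remains.
- If loss follows the unseen 12-month score in both arms (assumptions of step 4, true effect 3), using the 6-month score moves the estimate only from 3.49 to 3.36 at 25/15, and from 3.98 to 3.71 at 30/10.

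Under purely random 20% loss the gain is small: the standard errors are 0.769 and 0.753, and 0.753² / 0.769² = 0.96, about 4% less variance.

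**The case against.** Baseline-adjusted regression at the endpoint visit is a conventional primary model. It already tolerates loss that depends on arm, strata or baseline score. A longitudinal model is planned too, so a disagreement between the two analyses could come to light. Abandoning the platform is also not the same as failing to return the 12-month FPAS. All of this stands and limits the size of the concern. It does not remove it: the headline result still comes from completers, and as written the longitudinal model may be confined to the same patients. The analysis set and primary model are stated choices, not details left to a later analysis plan.

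Four stronger readings are tempting, and the document does not support them.
- *Different loss by arm is enough to bias the result.* It is not (step 4), and equal loss does not protect (step 2).
- *A bias of 0.7 points and a 14% type I error are to be expected.* Those values need dependence in the intervention arm only. Nothing in the document shows such a one-sided mechanism, and the same dependence in both arms gives 0.26 or less in the settings tabulated.
- *Using the 6-month score removes the problem.* Only if lost patients have that score and loss does not follow the unseen 12-month score.
- *The economic analysis uses everyone randomised, so the article contradicts itself.* The cost-effectiveness section says net benefit "will be analysed for the whole study population (intention-to-treat and per-protocol"), as opposed to subgroups. It does not say all randomised patients, and the only intention-to-treat set that the article defines is the modified one.

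**Conclusion.** The concern holds in a limited form. By its stated rule, the primary analysis excludes the expected 20% of patients without a 12-month evaluation and makes no use of their 6-month FPAS. Bias arises if loss is tied to post-baseline acceptance with a different strength or rate by arm. Under the assumptions in the working it lies between about 0 and 0.7 points, with type I error between 5% and about 14%. Only the SD, the 3-point target and the overall 20% loss come from the document. The correlations, loss slopes and split of loss by arm are assumed.

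The sign also rests on an assumption: the effect is overstated if poorly adapting patients leave the intervention arm, and understated if well-adapting patients do. This is a worthwhile and cheap improvement to the primary analysis. It does not show that the planned result will be wrong.

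**What to change.** 1. Make the longitudinal model the primary analysis. Fit it to all randomised patients, as randomised, who have a baseline and any post-baseline FPAS. Include visit by arm, baseline FPAS by visit and the strata, with an unstructured covariance. Take the month-12 arm contrast as the primary result.
2. State that the restriction to patients with a 12-month evaluation does not apply to this model.
3. Keep the 12-month completer regression as a sensitivity analysis.
4. Add a missing-not-at-random sensitivity analysis, for example one that shifts the unobserved 12-month scores by a range of amounts separately by arm. This covers patients with no 6-month score and loss that follows the unseen 12-month score.

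Cost: wording that changes the order of two analyses already planned, one added sensitivity analysis and a slightly more complex primary model. The sample size (382 evaluable, 478 randomised) and the visit schedule stay as they are. The article says a detailed analysis plan will be written before data are released, so the change can be made there.
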